**Table 1 T1:**
[figure not shown]
Participant timetable.

### Safety and monitoring

2.7

During the infusion, the patient will be monitored every 5 minutes for blood pressure (BP) levels, heart rate, peripheral oxygen saturation, respiratory pattern and level of consciousness. The patient will also be asked to report any other possible adverse event, not only during the intervention procedure, but at the subsequent visits at 24 hours, 72 hours, and 7 days after infusion. In case of elevated BP <30% of the pre-infusion levels, the infusion will be paused for 5 minutes and the patient evaluated for acute target organ damage. If there is no sign of acute complication and the BP levels drop, the infusion may continue and be completed.

Serious adverse events will be reported to the Ethics Committee of the hospital. The association of an event to the study drug will be evaluated based on a temporal and biological correlation analyses. As the intervention is conducted only once, blind will only be broken if strictly necessary and after discussion with the study senior coordinator.

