### Study settings and participants

2.2

The study will be performed in the Psychiatric Ward of [name] University Hospital (HUPES—Federal University of Bahia, in the city of Salvador) and São Paulo Hospital (Federal University of São Paulo, in the city of São Paulo) in Brazil. Both cities are among the largest urban areas in the country, with an ample variety of social, cultural, and ethnic characteristics, adequately reflecting the country's diverse population. Participants will also be referred from low and high complexity outpatient services, both public and private.

The study was approved by the local Institutional Review Board ([name] University Hospital—Federal University of Bahia—Number: 46657415.0.0000.0049). Current protocol version: 1.4, with past and possible future modifications always reported to the local IRB. Subjects will only participate after voluntarily agreeing and signing the informed consent form. The institutions in which the study procedures will be conducted will provide necessary hospital structure, drugs, and human resources. Additionally, a grant provided by the Programa de Pesquisa para o SUS (PPSUS) through Fundação de Amparo à Pesquisa na Bahia (FAPESB), a local public research-funding organization (Grant identification number: 5301/2017), will guarantee further resources. The funders had no role in study design, data collection, and analysis, decision to publish, or preparation of the manuscript.

This trial has been registered in the Japan Primary Registries Network (JPRN): UMIN000032355, which is affiliated with the World Health Organization (WHO).

Subjects will be males and females, aged 18 years or older, meeting all following inclusion criteria at the time of randomization: DSM-IV (Diagnostic and Statistical Manual of Mental Disorders version IV) MDD diagnosis confirmed with the Brazilian version of the Mini International Neuropsychiatric Interview 5.0.0 (MINI-Plus),^[22]^ characterized as TRD, defined by therapeutic failure after at least 1 adequate antidepressant treatment for at least 12 weeks. The exclusion criteria will be: concomitant treatment with electroconvulsive therapy, diagnosis of a psychotic disorder, mental retardation or dementia, unstable heart disease, and current illicit drug use.

All study-related information will be stored securely at the study sites in areas with limited access. Laboratory specimens will be identified by a coded identification to maintain participant confidentiality.

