### Intervention and group assignment

2.5

Participants will be submitted to a single dose of one of the 2 drugs in the study:

Ketamine racemic mixture (or ketamine hydrochloride):∘Dose: 0.5 mg/kg of body weight∘Commercial brand: Clortamina from Biochimico∘Dosing form: injectable solution, 10 mL ampoules, 50 mg/mLEsketamine (or S[+]-ketamine, or dextroketamine hydrochloride)∘Dose: 0.25 mg/kg of body weight∘Commercial brand: Ketamin from Cristalia∘Dosing form: injectable solution, 2 mL ampoules, 50 mg/mL

Both drugs will be diluted in 100 mL of saline solution and administered intravenously with an infusion pump for a total duration of 40 minutes. The dose of 0.5 mg/kg of ketamine is the most commonly used in trials for depression,^[3]^ as for esketamine, we chose the 0.25 mg/kg dose, as it is considered 2 times more potent than racemic ketamine as an anesthetic.^[7]^ Previous experience of our group pointed that a faster infusion of esketamine, 10 minutes, is associated with reduced tolerability because of intense dissociation,^[24,25]^ so we chose to use the standard 40 minutes’ duration.^[3]^

Participants will be randomized into esketamine and ketamine groups, on a 1:1 ratio, through an electronic randomization software http://www.randomizer.org platform. The only professionals with knowledge of the drug being infused are the investigator responsible for the allocation process, who will be only one for both centers, and a nurse responsible for drug preparation, one for each center. They do not participate in any clinical evaluations. As both drugs will be diluted in a saline bottle, it will not be possible to identify them visually. It is possible that the two forms of ketamine differ in terms of adverse effects, especially psychotomimetic, but those effects are very idiosyncratic and will help maintain the blinding of the study.

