### Secondary outcome measures

2.6

MADRS will also be performed 7 days after the intervention to access duration of remission. Treatment response, defined as ≥ 50% reduction in baseline score, will also be accessed with MADRS. The Global Clinical Impression (CGI) scale,^[26]^ will be an additional measure of efficacy.

Previous dissociative experiences will be assessed with a questionnaire, the Dissociative Experience Scale (DES),^[27]^ performed before the administration of the drug. To evaluate dissociative/confusional symptoms intensity, the Clinician-Administered Dissociative States Scale (CADSS)^[28,29]^ will be used. Assessment with CADSS will be initiated 20 minutes after the beginning of the infusion, as it is when dissociative symptoms start to rise.

Columbia-Suicide Severity Rating Scale (C-SSRS)^[30]^ will be used for assessing suicidality, and will be performed at baseline, then 24 hours, 72 hours, and 7 days after the infusion. Young Mania Rating Scale^[31]^ will only be performed in case of evident manic symptoms at any of the evaluation days. Finally, Medication Adherence Rating Scale (MARS)^[32]^ will be used to measure the psychiatric drugs adherence and performed at enrollment day.

To examine the relationship between clinical response and molecular and epigenetic mechanisms approximately 20 mL of blood will be collected to analyze serum levels of microRNA-206 and microRNA-1202, BDNF, IL-1B, IL-6, TNF-A, and other elements for the metabolomics profile at different timepoints.

Neuropsychological evaluations will be performed to measure cognitive functions: intelligence, executive functions (inhibitory control, cognitive flexibility, verbal fluency), attention, processing speed, memory and working memory (verbal and visual). Aspects related to personality will be analyzed based on the theory of Goldberg's Big Five factors of personality, using the NEO-FFI-R (NEO Five Factor Inventory Revised), a scale composed of 60 items that evaluate the five dimensions of the personality.^[33]^

The schedule of assessments and other procedures is summarized in Table 1.

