### Trial status

4.1

This trial is currently recruiting participants. Recruitment began on March, 2017. We expect the recruitment phase to be completed by the end of 2018. The study findings will be published in peer-reviewed journals and presented at national and international conferences when completed.

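### The blood-pressure rule for pausing the infusion is printed with its inequality reversed

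*Protocol article*

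**What the plan says.** Section 2.5 (Intervention and group assignment) has each drug "administered intravenously with an infusion pump for a total duration of 40 minutes". Section 2.7 (Safety and monitoring) states that during the infusion "the patient will be monitored every 5 minutes for blood pressure (BP) levels", along with other vital signs.

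The action rule follows in the same section: "In case of elevated BP <30% of the pre-infusion levels, the infusion will be paused for 5 minutes". What happens at the trigger is that "the infusion will be paused for 5 minutes and the patient evaluated for acute target organ damage". The condition for restarting is: "If there is no sign of acute complication and the BP levels drop, the infusion may continue and be completed".

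No other section restates this threshold or gives a different blood-pressure rule. Section 2.2 (Study settings and participants) identifies the governing document: "Current protocol version: 1.4, with past and possible future modifications always reported to the local IRB". Section 4.1 (Trial status) reports: "This trial is currently recruiting participants".

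**The concern.** A rule that interrupts dosing on rising blood pressure should act when the rise is large. This one, as printed, acts when the rise is below 30% and prescribes nothing when it reaches or passes 30%.

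What is at stake is participant safety, not inference. It is the only blood-pressure action rule in the article, and it governs a decision taken while the drug is running. If the same sign stands in the working documents, staff who follow it to the letter would interrupt infusions for trivial rises and would have no written instruction for the rises that matter. Since patients were being enrolled when the article was written, the working text needs checking.

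**Working it through.** There is no sample size, power or error rate to reproduce here. The check is a logical one, with simple arithmetic for scale.

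**Inputs.** From section 2.7: the trigger (an elevation, the sign <, and 30% relative to the pre-infusion level), the action (a 5-minute pause and an assessment for organ damage), the restart condition (no complication and a falling pressure) and the 5-minute reading interval. From section 2.5: the 40-minute infusion. The article gives no blood-pressure values, so the pre-infusion systolic pressure is assumed to be 120 mmHg, with a range of 110 to 140. The article does not say whether systolic, diastolic or mean pressure is meant; systolic is used only for illustration.

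**Reading 1: a rise of less than 30%.** The upper limit of the trigger is the pre-infusion value × 1.30.

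| Assumed pre-infusion systolic (mmHg) | × 1.30 (mmHg) | Printed rule pauses at | Printed rule silent at | Corrected rule pauses at |
|---|---|---|---|---|
| 110 | 143 | 111 to 142 | 143 or more | 143 or more |
| 120 | 156 | 121 to 155 | 156 or more | 156 or more |
| 130 | 169 | 131 to 168 | 169 or more | 169 or more |
| 140 | 182 | 141 to 181 | 182 or more | 182 or more |

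The printed and corrected rules select exactly opposite sets of elevated readings. A reading of 121 against 120 would pause the infusion and call for an organ-damage assessment; a reading of 160 would call for nothing.

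**Reading 2: a pressure below 30% of the pre-infusion value.** At 120 mmHg this is 0.30 × 120 = 36 mmHg, so the rule would act below 36 mmHg. That contradicts both the description of the pressure as elevated and the restart condition that it should fall.

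**Reading 3: sign reversed, a rise of 30% or more.** Every part of the rule now fits. The pressure is elevated, the rise is large enough to justify looking for organ damage, and restarting once it falls is sensible.

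**Could the sign be a text-extraction fault?** The article's other clinical thresholds print in the right direction: remission is a MADRS score of 7 or less (section 2.4), and section 2.6 has "Treatment response, defined as ≥ 50% reduction in baseline score". A general fault is therefore unlikely. A fault confined to this one character cannot be fully excluded from the text alone.

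**The case against.** The strongest reply is that this is a self-correcting misprint. A clinician would see what was meant from the surrounding words, the article condenses a fuller protocol that actually governs the sites, and nothing shows that staff infuse from the article. On that view it is a minor editorial matter. Part of this stands: the article does not show what version 1.4 or the site instructions say, and harm to any patient is not demonstrated. But the article states a specific dosing threshold and states it wrongly, which is different from leaving a detail to the full protocol.

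A second reply is that the literal rule is mainly over-cautious. With readings every 5 minutes, a gradual climb would meet the under-30% trigger on the way up and be paused before it reached 30%. Only a jump from no elevation to 30% or more between two readings would escape altogether. This is right as far as it goes, and it narrows the practical gap. It does not rescue a rule that pauses on trivial rises and is silent at the level where action is most needed.

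A third reply is that the text does not settle whether > or ≥ was intended. That is true, but the choice matters only at exactly 30%.

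**Conclusion.** The concern holds. Neither literal reading gives a workable safety rule, reversing the sign does, and nothing else in the article corrects it. Confidence in the misprint is high.

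Its practical size is unknown: with no blood-pressure or pause rates given, the number of affected infusions cannot be estimated. The mmHg figures rest on assumed pre-infusion systolic values and show only where the rule changes direction (156 mmHg at 120; 143 to 182 across 110 to 140). Nothing in the document shows an effect on the noninferiority margin, power, primary analysis or comparisons between arms. It should be fixed because it inverts the only stated blood-pressure action rule of a trial that was enrolling patients.

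**What to change.** Reword the trigger in section 2.7 as a blood pressure elevated by ≥30% above the pre-infusion level. Check that protocol version 1.4 and the instructions at both sites carry ≥ or >, and let version 1.4 settle which, if it is correct there. If those documents carry <, correct them and report the change to the IRB, as section 2.2 provides for modifications. If they are already right, correct the article only.

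The cost is one character for the sign (a few words if the phrasing is also changed to say above the pre-infusion level) and a check of version 1.4 and two sets of site instructions. No design or analysis element needs to change.

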## Statistical considerations

3

We selected a noninferiority margin of 20% based on clinical judgment. Assuming the control group would have a remission proportion of 30% based on literature data. Our board of experts deemed this a reasonable threshold to clinically consider using an intervention in TRD.

Assuming the intervention group to have a similar remission proportion of 30%, we calculated a sample size of 130 people (in both groups) would be needed to achieve 80% power with an alpha of 5% in the one-sided hypothesis test for efficacy. Owing to logistic constraints, we are limited to 96 patients, which brings our power down to 66%, keeping all other parameters constant. We decided to run the study even though underpowered upon starting the protocol, and to reassess power during the interim analysis.

All analyses will be conducted within the intention-to-treat (ITT) perspective. Intention-to-treat analysis can bias results in studies with active controls, but as the study intervention is a 1-time in-hospital drug infusion we expect no deviations from the randomized treatment. Summary statistics will be presented as means and standard deviations, medians, and interquartile ranges or frequencies based on variable distribution.

All the main analyses will be performed with univariate hypothesis tests. The main outcome (remission on the MADRS scale at 24 hours after infusion) will be analyzed by calculating a point estimate for the difference in remission proportion among the intervention and active control groups, and then by building a 1-sided 95% confidence interval. The null hypothesis will be rejected if the margin of this confidence interval is equal to or smaller than the noninferiority margin. All other secondary efficacy outcomes will also be analyzed by computing a bound for a 1-sided 95% confidence interval for parameter difference (means or proportion depending on variable distribution), with sensitivity analysis with 2-sided traditional hypothesis testing. All safety secondary outcomes will be compared with 2-sided hypothesis testing based on variable distribution (T test for normally distributed variables, *χ*^2^ or Fisher exact test for proportions).

We will perform an interim analysis for efficacy, futility, and safety upon reaching 50% of target enrollment (48 patients). We will adjust our alpha according to the Maybittle-Peto rule in the interim analysis for efficacy to avoid “alpha spending.” Futility will be assessed by calculating conditional power based on an exact method for calculating the joint probability of all scenarios of the final 2 × 2 table that reject the null hypothesis using binomial distributions and an indicator function for null hypothesis rejection.

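### The stated 66% power for 96 patients does not follow from the calculation that gives 130 for 80%; that calculation gives about 69%

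*Protocol article*

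**What the plan says.** All of the design inputs but one are in section 3 of the protocol article, Statistical considerations.

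- Margin: "We selected a noninferiority margin of 20% based on clinical judgment".
- Control arm: "Assuming the control group would have a remission proportion of 30% based on literature data".
- Esketamine arm: "Assuming the intervention group to have a similar remission proportion of 30" per cent, so the assumed true difference is zero.
- Error rate: "with an alpha of 5% in the one-sided hypothesis test for efficacy".
- Resulting size: "we calculated a sample size of 130 people (in both groups) would be needed to achieve 80% power".
- Size actually planned: "Owing to logistic constraints, we are limited to 96 patients, which brings our power down to 66%, keeping all other parameters constant".

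The planned analysis matches this set-up. It estimates the difference in remission proportions by "building a 1-sided 95% confidence interval" and compares the bound with the margin. The article names no interval method. Section 2.5 gives 1:1 allocation, so 130 means 65 per arm and 96 means 48 per arm. No attrition rate enters the calculation, and section 2.4 expects little missing data for the primary outcome.

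**The concern.** The two power figures stand in consecutive sentences, and the second claims to differ from the first only in the number of patients. If so, one formula with one set of inputs should return both. It returns the first exactly and misses the second.

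What is at stake is modest. The 66% is the only power figure given for the trial that is actually being run, and it tells ethics committees, funders and readers how far short of 80% the trial falls. That figure should be reproducible from the inputs beside it. At present a reader cannot tell whether it is a slip, the product of a different method, or the result of an input that was not reported.

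**Working it through.** **Inputs.** Remission p = 0.30 in both arms, margin 0.20, one-sided alpha 0.05 (z = 1.6449) and power 80% (z = 0.8416), all from section 3; equal allocation from section 2.5.

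**Step 1: reproduce the stated sample size.** For noninferiority of two proportions with unpooled variance and a true difference of zero:

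n per arm = (1.6449 + 0.8416)² × 2 × 0.30 × 0.70 / 0.20² = 6.183 × 0.42 / 0.04 = 64.92, rounded up to 65.

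The total is 130, as stated. Power at 65 per arm is Φ(0.20/√(0.42/65) − 1.6449) = Φ(2.4881 − 1.6449) = 80.0%.

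**Step 2: change only n.** At 48 per arm the standard error is √(0.42/48) = 0.09354, so

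power = Φ(0.20/0.09354 − 1.6449) = Φ(2.1381 − 1.6449) = Φ(0.4932) = 68.9%.

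The stated 66% is 68.9 − 66 = 2.9 points lower.

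**Step 3: is it rounding?** Solving the same formula for 66% gives 44.4 per arm. Power is 65.6% at 44 per arm and 66.5% at 45, so 66% corresponds to roughly 88 to 90 patients, not 96.

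**Step 4: does another standard method give both figures?**

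| Method | Power at 96 | Power at 130 | Total N for 80% |
|---|---|---|---|
| Unpooled normal approximation | 68.9% | 80.0% | 130 |
| t-based | 68.4% | 79.7% | not computed |
| Farrington-Manning formula | 69.4% | 80.4% | not computed |
| Exact unconditional test ordered by the Farrington-Manning statistic | 68.8% | 80.1% | not computed |
| Binomial enumeration, Wald interval | 70.0% | 80.6% | not computed |
| Binomial enumeration, Newcombe interval | 71.3% | 81.4% | not computed |
| Null variance at 0.5 and 0.3 | 66.2% | 77.8% | 138 |
| Continuity correction 1/(2n) | 64.9% | 77.3% | 140 |
| Continuity correction 1/n | 60.7% | 74.3% | 150 |
| One-sided alpha 0.025 | 57.1% | 70.1% | 166 |

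The first six methods are at or near 80% at 130 patients and give 68% to 71% at 96. The methods that come close to 66% at 96 fall below 78% at 130 and need 138 or 140 patients for 80%. No method tried returns both published figures.

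**Step 5: could the interim look explain it?** Spending some alpha early would lower the power, but a final one-sided alpha of 0.049 still gives 68.6%. Reaching 66% would need a final alpha between 0.040 (65.1%) and 0.045 (67.1%). The article states no such reduction, and it would itself be a changed parameter.

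**The case against.** The strongest objection is that this hardly matters. The plan understates its power, so no one is misled in the optimistic direction. The article openly says that the study starts underpowered, and that is equally true at 66% and at 69%. All of this stands, and it limits the point to a small correction.

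Four stronger readings are tempting, and the document does not support them.

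- A reader might infer that the 66% was the reason for going ahead with 96 patients. Section 3 attributes the 96 to practical limits and reports the power as a consequence. Nothing suggests that 69% would have led to a different decision.
- A reader might infer that the wrong figure carries into the interim analysis, since section 3 says power will be reassessed there. The futility method at the end of that section computes conditional power from binomial probabilities over the possible final 2 × 2 tables. The 66% is not an input to it or a threshold in it.
- A reader might infer an undisclosed loss of about 6% to 7%, because about 90 evaluable patients would give roughly 66%. The article states no such allowance, says that the other parameters were held constant, and expects little data loss. It is a possible explanation, but nothing in the text shows it.
- A reader might put the gap at up to 5 points by using the 70% to 71% from binomial enumeration. Those figures depend on the interval chosen, which the article does not name, and the exact unconditional test gives 68.8%. The fair comparison is with the calculation that reproduces 130, and there the gap is 2.9 points.

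None of this recovers the 66%.

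**Conclusion.** The point holds as a minor arithmetic error. Under the calculation that reproduces 130 patients for 80% power, 96 patients give 68.9%, so the stated power is about 3 points too low. The sample size of 130 is correct for its inputs. The error is conservative and leaves the planned 96 patients, the margin, the analysis and the decision rule unchanged.

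This rests on equal arms of 48, all 96 patients evaluable, 30% remission in both arms, and the unpooled normal approximation. The article does not name that method; it is inferred because it returns the stated 130 exactly. The other methods consistent with 130 stay between 68% and 71% at 96, so the conclusion does not depend on that choice.

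**What to change.** In section 3, restate the power as about 69% with 96 evaluable patients, and name the method used for both this figure and the 130.

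If the 66% was obtained with a different input, such as an allowance for loss, state that input and remove the clause saying that the other parameters were unchanged. It should then also be clear whether the 130 carries the same allowance.

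The interim conditional power needs no change. The cost is one number and a few words, with no operational consequence.

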### Study design

2.1

The present trial is a prospective, randomized, controlled, intervention, double-blind, noninferiority study, with 2 parallel groups, that will include a total of 96 individuals, with a follow-up duration of 7 days after randomization. Patients will maintain naturalistic treatments (not changing dose or type of medicine) until 15 days before the randomization; this should minimize potential biases caused by differences between groups, but they may not have new drugs included in their treatment regimen during the study week (except for non-benzodiazepine sleep inducers). After completion of the study week, patients will continue under the most convenient treatment regimen.

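### ITT is the only analysis set for the noninferiority claim, on an expectation of no deviations that the protocol's conditional infusion-completion rule undermines

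*Protocol article*

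**What the plan says.** Section 3 (Statistical considerations) fixes the analysis population in one sentence: "All analyses will be conducted within the intention-to-treat (ITT) perspective". The next sentence acknowledges that ITT can be a source of bias when the comparator is active, and gives the reason for going no further: "as the study intervention is a 1-time in-hospital drug infusion we expect no deviations from the randomized treatment". No per-protocol or other supporting set is named.

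Two other sections bear on that reason. Section 2.7 (Safety and monitoring) provides for a five-minute pause of the infusion when blood pressure rises, and then says: "If there is no sign of acute complication and the BP levels drop, the infusion may continue and be completed". Section 2.1 (Study design) restricts concomitant treatment: "they may not have new drugs included in their treatment regimen during the study week", with non-benzodiazepine sleep inducers exempted.

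**The concern.** In a superiority trial, patients who do not receive the treatment as assigned usually pull the arms together and make a positive claim harder. In a noninferiority trial the same dilution makes the claim easier, which is why ITT alone is not regarded as the cautious choice there. The protocol names this problem and then relies wholly on its not arising.

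Section 2.7 shows that it can arise. If the stated conditions are not met after a pause, nothing in the text provides for completion, and that patient will have had less than the assigned dose. The protocol therefore foresees in one section an event that it expects not to see in another. If such events occur, the plan has no analysis to show whether a noninferiority finding reflects similar efficacy or dilution. The stake is a false conclusion that esketamine is no more than 20 percentage points worse.

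**Working it through.** **Inputs from Section 3.** Margin 20 percentage points ("We selected a noninferiority margin of 20% based on clinical judgment"); ketamine remission 30%; esketamine remission assumed equal for the sample size; one-sided alpha 5%; 130 patients for 80% power; 96 patients planned. Section 2.5 gives 1:1 allocation, hence 48 per arm.

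**Inputs that I assume.** Section 3 expects no deviations and the documents give no rate. I use a share *d* of 5%, 10% or 15%, and a remission rate among deviators of 10% or zero. These are illustrations, not estimates.

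**Step 1: reproduce the plan's sample size.** With the unpooled normal approximation,

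n per arm = (1.645 + 0.842)² × (0.30×0.70 + 0.30×0.70) / 0.20² = 6.18 × 0.42 / 0.04 ≈ 64.9, so 65 per arm and 130 in total, as stated.

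At 48 per arm the standard error is √(0.42/48) = 0.0935, and power is Φ(0.20/0.0935 − 1.645) = Φ(0.493) = 68.9%. Exact enumeration gives 70.0%. The protocol states 66%. The small gap does not affect this point.

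**Step 2: the decision rule.** Noninferiority is declared when the upper one-sided 95% bound for ketamine minus esketamine does not exceed the margin:

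(p̂_K − p̂_E) + 1.645 × √[p̂_K(1−p̂_K)/48 + p̂_E(1−p̂_E)/48] ≤ 0.20.

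Section 3 does not name the interval method; I take the Wald bound, in line with the formula that reproduces 130. The type I error is the probability of this event when the true difference equals the margin, here 30% versus 10%, summed over all pairs of binomial counts.

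**Step 3: mix deviators into the ITT rates.**

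- A. Both arms, deviators remit at 10%: ketamine 0.30(1−d) + 0.10d; esketamine stays at 0.10.
- B. Ketamine arm only, deviators do not remit: ketamine 0.30(1−d); esketamine 0.10.
- C. Esketamine arm only, deviators do not remit: ketamine 0.30; esketamine 0.10(1−d).

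| Share d | A: both arms | B: ketamine only | C: esketamine only |
|---|---|---|---|
| 0 | 5.3% | 5.3% | 5.3% |
| 5% | 6.8% | 7.7% | 4.6% |
| 10% | 8.6% | 10.9% | 4.1% |
| 15% | 10.9% | 15.1% | 3.6% |

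For example, at d = 10% in A the ketamine rate is 0.27 + 0.01 = 0.28, the ITT difference shrinks from 20 to 18 points, and the error is 8.6%. With one deviator per arm (1/48, about 2%), A gives 5.9%.

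**Step 4: precision of a per-protocol analysis.** If 10% per arm were excluded, about 43 per arm would remain. With equal 30% rates, power on that set is about 65%, against about 70% at 48 per arm (both exact).

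**The case against.** The best defence is that the authors raised the issue themselves and answered it with a feature of the design: a single supervised dose leaves no adherence period in which patients can drift off treatment. If deviations are as rare as they expect, the effect is negligible; one per arm moves the error only from 5.3% to 5.9%. Supporting analysis sets are also ordinary content for a statistical analysis plan, which is not shown. The first part stands as a limit on the size. The second does not remove the point, because Section 3 assigns all analyses to ITT and argues why that suffices. That is a stated choice, not a detail left open.

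A reader might infer more than the text supports in three respects.

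- That Sections 2.7 and 2.1 contradict the expectation of no deviations. They do not. A pause followed by completion is conduct that the protocol prescribes. The no-new-drug rule is a prohibition; only a breach would be a deviation, and one of concomitant treatment. Section 3 sets the main outcome at 24 hours, which leaves little time for a breach to matter, though Section 2.4 also lists 72 hours.
- That deviations always favour noninferiority. Column C shows the reverse when they fall only on esketamine. Section 4 suggests that esketamine may be less dissociative, which would make interrupted ketamine infusions the likelier pattern, but no passage links dissociation to stopping an infusion.
- That missing ratings counted as non-remission add to the bias. The article states no such rule, and the handling of missing data may be left to a document not shown.

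**Conclusion.** The point holds as a should-fix item. For a noninferiority claim the protocol relies on ITT alone, after conceding the bias that ITT can bring, and its only reason is an expectation that the conditional completion rule in Section 2.7 makes unsafe. Similar deviations in both arms at an assumed 5% to 15% would raise a nominal 5% error to roughly 7% to 11%. Deviations confined to ketamine would raise it further, and deviations confined to esketamine would lower it below the baseline. These figures rest on assumed deviation rates, assumed remission among deviators, the Wald bound, and true rates of 30% versus 10%. They show that the check is worth having; they do not show that this trial's error is inflated.

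**What to change.** Keep ITT as the primary analysis. In Section 3, add a per-protocol analysis of the primary endpoint, limited to patients who received the full assigned infusion, took no prohibited new drug before the rating, and have the rating. Fix the definition before unblinding, report the result beside ITT, and state any disagreement between the two when concluding on noninferiority. Replace the expectation of no deviations with a commitment to record and report incomplete infusions by arm.

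The cost is one deviation flag per patient and one further analysis. If the authors' expectation is right, the two sets coincide and nothing changes. If it is wrong, the per-protocol result is somewhat less precise. It is also open to selection after randomization, since whether an infusion is completed depends on a blood-pressure response that may differ by drug. For that reason it should support ITT and not replace it. I do not propose that both sets must clear the margin: that would cost power in a trial that already acknowledges being underpowered.
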